**Table 2: Definition of severity for gastrointestinal symptoms**

| Symptom           | Moderate                                                                                               | Severe                                                                                                               |
|-------------------|--------------------------------------------------------------------------------------------------------|----------------------------------------------------------------------------------------------------------------------|
| Nausea     | Affects the subject's normal daily activities.                                                         | Prevents the subject's normal daily activities or requires confinement to bed.                                       |
| Vomiting*  | More than 4 episodes in a 24-hour period but no evidence of clinically significant dehydration.        | More than 6 episodes in a 24-hour period or evidence of significant dehydration as a result of the vomiting.         |
| Diarrhoea* | More than 4 unformed stools in a 24-hour period but no evidence of clinically significant dehydration. | More than 6 unformed stools in a 24-hour period or evidence of significant dehydration as a result of the diarrhoea. |

\* If the number of episodes are not reached but hospital admission is required, the event will still be classified as severe, as well as classifying as a Serious Adverse Event.

**Table 3: Definition of severity for laboratory value abnormalities**

| Laboratory test                           | Moderate                          | Severe                     |
|-------------------------------------------|-----------------------------------|----------------------------|
| WBC increase                       | = 15 to 20 x 10  /L   | > 20 x 10  /L  |
| WBC decrease                       | < 2.5 to 1.5 x 10  /L | < 1.5 x 10  /L |
| Liver function tests (AST and ALT) | 2.5 to 3.5 x ULN*                 | > 3.5 x ULN*               |

\* ULN = Upper Limit of Normal

In the event of a *salmonella* bacteraemia, dosing will be suspended until it has been determined whether the strain responsible for the bacteraemia is *S. typhi* (Ty2 *aroC* *ssaV*) ZH9. If it is determined that the bacteraemia should be attributed to *S. typhi* (Ty2 *aroC* *ssaV*) ZH9 or the vaccine strain cannot be ruled out as the causative agent, dosing will be suspended and an SAE report will be provided to the FDA and other relevant regulatory authorities.

Other signs and symptoms may also lead to suspension of dosing or other changes in the intended protocol pending review of the safety data and culture results.

#### **4.8.2 Individual Subjects**

If a subject wishes to leave the study at any time, or if either of the subject's parents or guardians withdraw their permission, the subject will be permitted to leave the study without any penalty. The collection of safety data is important for the safety of the individual subject and therefore, subjects who withdraw will be encouraged to monitor their temperature and adverse events and return for safety follow-up and the collection of samples for reasons of safety. It will be stressed to the subject and his/her parents or guardians that if the subject becomes unwell they should, at a minimum, contact the investigative site and preferably visit the investigative site to ensure the vaccine has not caused any adverse events.

#### **4.9 Randomisation Codes and Breaking the Code**

Subjects will be allocated a 'Screening Number' on entry into the study (signature of the written permission document). This number, together with their initials will be used to identify them until they are deemed eligible to receive study treatment at Visit 1.

At Visit 1, all subjects eligible to receive study treatment will be allocated a unique subject number (this number will be recorded in the Visit 1 CRF together with the Screening Number; at subsequent visits, the subject will be identified by this number and their initials only). This number will be allocated strictly sequentially (within each age-group cohort) in accordance with the randomisation schedule. The randomisation schedule will determine if a subject receives vaccine or placebo. The vials of IMP will be provided to the study site pre labelled with subject numbers.

Code break will be provided to the Investigator. The code for a particular subject can be broken in a medical emergency if knowing the identity of the treatment allocation would influence the treatment of the subject. Whenever a code is broken, the person breaking the code must record the time, date and reason as well as their initials in the source documents.

If the site needs to break the code, the sponsor should, if possible, be contacted prior to breaking the code. In all cases, the Study Monitor must be notified within 24 hours after the code has been broken.

All code break (whether broken or not) must be kept throughout the study period. Codes will be checked for integrity and collected by the Study Monitor at study site closure.

---

## 5 SELECTION AND WITHDRAWAL OF SUBJECTS

### 5.1 Inclusion Criteria

Subjects must satisfy the following criteria

1. Healthy paediatric subjects aged 5 to 14 years inclusive, of Vietnamese origin, who are able and willing to take part in the trial and whose parents or guardians give written permission for their child's participation, following a detailed explanation of the study.
2. Subjects who will be available for the duration of the study and available for scheduled and potential additional visits.

### 5.2 Exclusion Criteria

Subjects meeting any of the following criteria must be excluded from the study

1. Subjects with any clinically significant medical or psychiatric condition or clinically significant abnormal serum biochemistry or haematology results that, in the opinion of the Investigator, preclude participation in the study.
2. Subjects whose body weight is under 17kg (5-10 year olds), or under 27kg (11-14 year olds)
3. Female subjects who are pregnant (confirmed with urinary pregnancy test) or breast-feeding, or of childbearing potential and unwilling to use a reliable method of contraception (oral contraceptives, barrier method with spermicidal preparation or abstinence) throughout the study period.
4. Subjects who have a known hypersensitivity to two or more of the following antibiotics; ciprofloxacin, azithromycin or trimethoprim-sulfamethoxazole or have used antibiotics/antibacterials within 14 days prior to administration of study medication.
5. Subjects who have a known hypersensitivity to any component of the vaccine or bicarbonate solution used in this study, including subjects with phenylketonuria or those who have experienced anaphylactic shock after any vaccination.
6. Subjects who received Vivotif, either as a licensed or investigational product, in the last 10 years or any other vaccine against *S. typhi*, whether licensed or investigational, in the last 5 years, or who have ever suffered from typhoid fever.
7. Subjects with direct contact with patients in special care units or immuno-compromised individuals.
8. Subjects who have a positive bacterial culture of their faecal sample, obtained at the screening visit, for any *Salmonella* species.
9. Subjects with a known impairment of immune function including acquired immune deficiency syndrome or those receiving (or having received in the 6 months prior to screening) cytotoxic drugs, immunosuppressive therapy (including systemic corticosteroids).
10. Subjects who are HIV positive or have family members who are HIV positive. ('Family members' includes immediate and extended family living in the same residential unit, or relations with whom the subject has regular and frequent contact).

11. Subjects with a significant acute febrile illness (body temperature of 38.0°C or more) at time of dosing.
12. Subjects who have chronic diseases: Chronic diseases will include all autoimmune and immuno-compromising conditions and any other chronic condition which, at the judgement of the Investigator, may put the subject at higher risk of side effects from the study vaccine. Conditions in the latter category might include unexplained anaemia, hepato-biliary disease, uncontrolled hypertension, subjects with prosthetic joints or heart valves, etc.
13. Subjects with a current problem, based on history, of substance abuse or with a history of substance abuse that, in the opinion of the investigator, might interfere with participation in the study.
14. Subjects who are currently involved in a clinical study, have taken an investigational drug or have received investigational or licensed vaccines in the 4 weeks before screening, or anticipate receiving a vaccine, other than study medication, during the first 4 weeks, post vaccination, of the study.

Subjects excluded for medical reasons will be referred to appropriate medical care services or counselling.

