#### 4.7 Duration of Subject Participation

Each subject's participation in the study will be for up to 28 days during the screening period plus 28 days following the administration of the investigational medicinal product (IMP), making a total of 56 days. Recruitment of 150 subjects at the study site is expected to take approximately six months.

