## **6.6 Concomitant Medication**

The use of all medication including ‘over the counter’ and herbal products taken in the 4 weeks prior to screening and during the course of the study, up to Day 28, must be detailed in the case report form (CRF). Subjects are to try to avoid all antibiotic/antibacterial use for 14 days before and after dosing. Should a subject require antibiotics he/she must inform the Investigator and may be withdrawn from the study depending on the timing in relation to the vaccination or have their data excluded from the PP analysis. Subjects must not receive any vaccine other than M01ZH09 during the four weeks, post dose, of the study.

Oral contraception is allowed under the protocol. However, should a female subject using oral contraception develop diarrhoea or require antibiotic therapy she will be requested to use additional barrier methods of contraception in combination with a spermicidal preparation.

If a subject has

- a single positive blood culture, or
- a positive stool culture for *S. typhi* at any time after Day 7

he/she must be treated with antibiotics. The first line antibiotic will be ciprofloxacin 20 mg/kg twice daily, taken orally for 10 days. The second line antibiotic will be azithromycin. The dose of azithromycin is dependent upon the age of the subject. Subjects aged 5 to 7 years should receive 5 mL (200 mg) orally once daily for 7 days, subjects aged 8 to 11 years should receive 7.5 mL (300 mg) orally once daily for 7 days and subjects 11 to 14 years should receive 10 mL (400 mg) orally once daily for 7 days. The third line antibiotic is trimethoprim 40 mg/sulfamethoxazole 200 mg per 5 mL of suspension twice daily, 10 mL taken orally for 10 days. In all cases antibiotic therapy will be initiated as soon as the culture results are known.

Any subject who returns for unscheduled visits after Day 14 and has positive blood or stool cultures for *S. typhi* will be treated as a potential carrier and treated with antibiotics and followed up until the infection is clear. Antibiotics will be administered as outlined above at the discretion of the Investigator. The duration of treatment may be up to 28 days to ensure the infection is clear.

The vaccine strain has been shown to be sensitive to ciprofloxacin, azithromycin and trimethoprim/sulphamethoxazole. Ciprofloxacin has been shown to be the treatment of choice for chronic carriers of wild type *S. typhi*.

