## **6.8 Visits and Procedures**

### **6.8.1 Screening period (Day –28 to Day –1)**

The parents or guardians of all subjects will provide written permission before any study related procedure is carried out. Where appropriate, with regard to age and understanding, the subject will be asked to sign an assent form indicating their willingness to take part in the study. After written permission has been obtained, the subject will be allocated a 'Screening Number' which will be used, together with his/her initials as their unique identifier until dosing at Visit 1. The following will be recorded/performed:

- Demographic data
- Medical history, including any allergies, and vaccination history
- Prior concomitant medications (in previous 4 weeks before screening), particularly antibiotic use and including herbal and over the counter medications
- Physical examination including height, weight and vital signs (blood pressure, temperature and pulse) and an examination for any signs of splenomegaly.
- Draw blood for:
  - Serum biochemistry and haematology (Section 7.2.1)
  - HIV test
- Obtain urine sample for:
  - Urine pregnancy test (females of 11 years and older only)
  - Dipstick test, and if the dipstick is positive for leucocyte esterase and nitrites, a separate sample will be sent for microscopy, culture and sensitivity
- Obtain stool sample for culture for *Salmonella spp.*
- Make an appointment for suitable subjects to attend for Visit 1 (randomisation and administration of the study medication) within the next 4 weeks. Instruct subject to bring a stool sample to the next visit.

### 6.8.2 Visit 1: Day of Dosing/ Day 0

This visit should take place within 28 days of the screening visit, following receipt of the full laboratory results. After the laboratory results have been reviewed, those subjects who continue to meet the inclusion criteria, and do not meet any of the criteria for exclusion, will continue in the study. The following tasks will be performed:

- Collect stool sample subject has brought to clinic. (Note: This sample will not be cultured prior to dosing but if it is subsequently shown to be positive for any Salmonella strain the data from the subject will be excluded from the PP analysis).
- Review the inclusion and exclusion criteria for continued study eligibility
- Review medical history and record any changes since screening

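### Exclusion 14 counts its vaccine washout back from screening, so a licensed non-typhoid vaccine given in the up to 28 days between screening and dosing meets no stated rule

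*Protocol*

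**What the plan says.** Two parts of exclusion 14 (section 5.2; same wording in the synopsis) concern other vaccines. A child is excluded who is found to "have received investigational or licensed vaccines in the 4 weeks before screening", or to "anticipate receiving a vaccine, other than study medication, during the first 4 weeks, post vaccination, of the study". Section 6.6 adds a ban that starts at dosing: "Subjects must not receive any vaccine other than M01ZH09 during the four weeks, post dose, of the study".

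Screening and dosing are separate visits. Section 6.8.2 says of Visit 1: "This visit should take place within 28 days of the screening visit". Section 4.7 gives the same span, setting participation at "up to 28 days during the screening period plus 28 days following the administration" of the product.

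At Visit 1 the staff must "Review the inclusion and exclusion criteria for continued study eligibility", go over the medical history and concomitant medication again, and record changes since screening. A delay-or-withdraw rule follows for two findings only: antibiotic therapy in the preceding 14 days, and an oral temperature of 38°C or more.

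The antibiotic criterion, exclusion 4, uses a different anchor. It rejects children who "have used antibiotics/antibacterials within 14 days prior to administration of study medication".

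**The concern.** The protocol evidently wants other vaccines kept away from the study dose on both sides. The later side is measured from dosing, but the earlier side is measured from screening, which can lie four weeks before dosing. A child vaccinated between the two visits falls in neither window.

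At stake is how clean the safety data are. One secondary safety endpoint is a temperature of 38.5°C or more in the 14 days after dosing, attributed to study medication. A reaction to another vaccine given shortly before Day 0 could appear in those 14 days, and the investigator would then have to judge between two recent exposures. The fever counts in Table 1 (section 4.8.1), which trigger suspension of dosing, carry no attribution condition, so such a fever would count there whatever its cause.

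**Working it through.** No sample size, power or error rate is involved. The check is a count of days, followed by a search of the protocol for any other rule that fills the gap.

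**Inputs**
- Washout before entry: 4 weeks = 28 days, counted back from screening (exclusion 14).
- Screening to dosing: s days, with s from 1 to 28 (sections 4.7 and 6.8.2).
- Ban after dosing: four weeks (section 6.6; second vaccine clause of exclusion 14).

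**Coverage of the 28 days before dosing**

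Put dosing on Day 0 and screening on Day −s. The washout covers Day −(s + 28) up to screening. Of the 28 days just before dosing, it therefore covers 28 − s and leaves s uncovered.

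| s (days from screening to dosing) | Covered | Uncovered |
|---|---|---|
| 1 | 28 − 1 = 27 | 1 |
| 14 | 28 − 14 = 14 | 14 |
| 28 | 28 − 28 = 0 | 28 |

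If the same 28 days were counted back from dosing, all 28 would be covered for every s.

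**Does another rule close the gap?**
- *Eligibility review at Visit 1 (6.8.2).* It re-reads the same criterion. The look-back still ends at screening, so a later vaccine does not meet it.
- *History review at Visit 1 (6.8.2).* The screening history includes vaccination history (6.8.1), and changes since screening are recorded. An interval vaccine should therefore be written down, but no action follows.
- *Deferral rules at Visit 1 (6.8.2).* They cover antibiotics and temperature only. A vaccine reaction that already shows as 38°C on Day 0 would be caught; one that has not yet appeared would not.
- *Withdrawal for treatments not permitted (5.3).* This refers to section 6.6, where the vaccine ban begins at dosing.
- *Exclusion 6.* Its limits of 10 years for Vivotif and 5 years for other *S. typhi* vaccines are not tied to screening, so a typhoid vaccine in the interval is still caught.
- *Current-trial clause of exclusion 14.* An investigational vaccine given within a running trial is still caught at the Visit 1 review.

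What remains open is mainly licensed non-typhoid vaccines.

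**The case against.** The strongest reply is that the gap is narrow and its consequences are diluted.

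- *Which vaccines.* A reader might infer that no vaccine given in the interval excludes a child. That goes too far: exclusion 6 and the current-trial clause of exclusion 14 still apply on Day 0. This limit stands.
- *Awareness.* The Visit 1 history review already brings an interval vaccine to the investigator's notice. Section 5.3 also allows withdrawal for safety concerns or in the child's best interest. Both are true, but discretion is not an eligibility rule, and the protocol did attach fixed rules to antibiotics and temperature.
- *Bias.* A reader might infer that the comparison of arms is distorted. The trial is randomised, and section 4.2 says that placebo measures background adverse events. Stray reactions should fall on both arms in proportion to their size. In addition, the relationship scale in 8.1.4 lets an investigator who knows of the other vaccine rate an event as unlikely to be related. What is left is noise and attribution error.
- *Immune response.* A reader might also infer that the immunogenicity results are at risk. Every immune endpoint in 3.4 is specific to *S. typhi* LPS, and the protocol gives no mechanism by which a non-typhoid vaccine would alter it. That inference is not supported.
- *Anchor.* Exclusion 9 also looks back from screening, and the antibiotic anchor has a reason of its own, since the live strain is sensitive to the named antibiotics (6.6). A different anchor is therefore not by itself an error. Yet exclusion 9 separately covers current treatment, whereas the vaccine wording has nothing for the interval, and no reason for leaving it open is given.
- *Analysis plan.* Section 9.2.3 leaves the per-protocol criteria to the SAP, which may deal with interval vaccines. That would not affect the safety summaries, which section 9.3 places on all dosed children.

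**Conclusion.** The gap is real and its extent is certain from the text: 1 to 28 uncovered days, up to the full length of the washout, for licensed non-typhoid vaccines. The 28-day figure applies only to a child dosed on the last permitted day.

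The effect is not certain. The protocol gives no vaccination rate for the interval and no distribution of screening-to-dosing times, so neither the number of children affected nor the number of extra fevers can be derived. The conclusion does not depend on either. It rests on reading exclusion 14 as written when it is reviewed on Day 0, and on there being no further rule in documents not shown.

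This is a minor point. No endpoint definition or between-arm comparison is invalid because of it. It is worth correcting because the rule as written admits children with a competing explanation for early fever and other adverse events, in a trial whose safety endpoints depend on attribution.

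**What to change.** Reconcile exclusion 14, in section 5.2 and the synopsis, with the dosing-anchored antibiotic criterion and the post-dose vaccine ban, so that the vaccine window runs without a gap to administration of study medication. Attach that rule to the existing Visit 1 review, which already asks the question. If the interval is meant to stay open, say so and give the reason.

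The sponsor should say whether the present look-back is moved to dosing or kept and extended to dosing. Moving it would admit some children whom the present text excludes, for example one vaccinated shortly before screening and dosed 28 days after it. The length of the window is for the sponsor to settle.

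The cost is one phrase in two places and one line at Visit 1, plus some rescheduling or re-screening. If a 28-day window is counted back from dosing, a child vaccinated v days after screening (v ≥ 1) could be dosed no earlier than 28 + v days after screening. That exceeds the 28-day limit, so such a child would need re-screening rather than a short delay. The re-screening provision in 6.8.2 is tied to the antibiotic and temperature cases and would have to be extended to this one.

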### **5.3 Withdrawal Criteria**

Emergent Product Development UK Ltd or the Investigator may decide to stop the study or part of the study at any time. If a study is prematurely terminated or suspended, the Investigator should promptly inform the subjects and ensure appropriate therapy and follow-up. Furthermore, the Investigator should promptly inform the Ethics Committee and provide a detailed written explanation. The pertinent regulatory authorities must be informed according to the national regulations.

A subject may be withdrawn from the study at the discretion of the Investigator or the Sponsor, if judged non-compliant with study procedures or due to safety concerns.

A subject must be withdrawn if any of the following apply:

- The wish of the subject or either of his/her parents or guardians
- Intolerable adverse event(s)
- Clinically significant abnormal laboratory findings (which in the opinion of the Investigator and/or Sponsor precludes further participation in the study)
- Non-compliance, (subject does not attend a minimum of 3 visits post dosing)
- Use of treatments not permitted during the study (see section 6.6)
- Investigator's decision that withdrawal from further participation would be in the subject's best interest.
- Pregnancy. Any subject who becomes pregnant will be followed up to determine the outcome of the pregnancy. The Investigator will be required to inform Emergent Product Development UK Ltd of a subject's pregnancy and the estimated date of delivery. Emergent Product

Development UK Ltd will follow up with the Investigator around the estimated time of delivery to determine the outcome of the pregnancy.

This is a single dose study; therefore subjects withdrawing after dosing would not be scheduled to receive any additional medication. Blood draws for immunogenicity assessments would be discontinued, although safety assessments would be continued. The collection of safety data is critically important and therefore subjects will be encouraged to return for the collection of samples for safety, whether they have been withdrawn for reasons of safety, have withdrawn their assent or have had their parental permission withdrawn. As many safety samples as possible will be collected.

